#### APACHE II Score

The APACHE II (Acute Physiology and Chronic Health Evaluation II) scoring system has high sensitivity and exhibits a negative predictive value in predicting pancreatic necrosis and organ failure. This makes it an ideal prognostic tool for assessing the severity of AP and in guiding clinical decision-making, particularly in resource-limited countries [19]. It is determined using the following formula:

APACHE II = (original score – current score)/original score × 100%

#### Modified Marshall Score

Organ failure plays a significant role in the severity of AP. The revised Atlanta classification recommends the use of the modified Marshall scoring system as the primary tool for assessing organ failure. The modified Marshall scoring system encompasses scoring systems for respiratory, cardiovascular, and renal systems to evaluate organ dysfunction in AP [6].

#### Levels of Inflammation Factor

The level of an inflammation factor is a surrogate marker for important clinical end point variables in AP. Multiple studies have shown that C-reactive protein is a good surrogate marker for SAP [20,21]. Additionally, interleukin (IL)–6 is superior in predicting SAP compared to other commonly used markers such as erythrocyte sedimentation rate. The level of an inflammation factor can be determined using the following formula [22]:

Inflammation factor = (original figure – current figure)/original figure × 100%

We will also use IL-1, IL-4, IL-8, and IL-10 to investigate the potential targets of DaXianXiong decoction. In pancreatitis, cytokines such as tumor necrosis factor–α secreted by acinar cells and damage-associated molecular patterns play a major role in activating immune cells such as neutrophils and macrophages. This process leads to increased pancreatic damage, systemic inflammation, and the development of SAP [8,23].

#### Gastrointestinal Dysfunction Treatment Effect

A comprehensive assessment of the gastrointestinal function is essential for the early detection of SAP. This assessment involves evaluating symptoms such as abdominal pain, distention, hematemesis, hematochezia, number of independent defecations, and digestive function. Signs such as tenderness, rebound tenderness, muscle tension, and the number of bowel sounds are also considered. Additionally, scores such as the gastrointestinal function score used in multi-organ dysfunction syndrome diagnostic criteria can provide a standardized measurement of gastrointestinal function.

#### Other Measures

Given the constraints of ethics and experimental techniques, certain indicators are valuable for assessing the improvements and prognosis of patients with AP. These include the time to bowel sound recovery, time to first defecation, and the gastrointestinal function score. These measures provide predictive information regarding gastrointestinal function and can be useful in evaluating the prognosis of patients with AP. We will also record hospitalization costs and duration.

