### Withdrawal Cases

Patients can withdraw from the study at any point without any repercussions. If a patient discontinues the intervention or decides to participate in another study, they will no longer be included in the present study. However, even when a patient withdraws from the study, the data collected up to that point will be retained and included in the analysis, unless specifically requested otherwise. The withdrawal and noncompliance of patients will also be documented. Incomplete data will be addressed based on the withdrawal rate. If the rate is <5%-10%, we will perform data cleaning. If the withdrawal rate exceeds 10%, the missing data will be managed through imputation, intention-to-treat analysis, and sensitivity analysis.

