### Sample Size

We will use preset sample sizes (*n*) determined using the following formula:

Where *μ*_1_ and *μ_2_* are the means of the intervention and placebo groups, respectively, and *σ* is the SD. The study aims to maintain the type I error probability (*α*) to <5% and the type II error probability (*β*) to <10%, with the *α* at .05 and the *β* at .1. To determine the sample size, we referred to literature reports in Chinese [24] on the use of DaXianXiong decoction for the treatment of AP. We used the time blood amylase took to return to normal levels to determine the clinical efficacy of the decoction. We fixed the total sample size for the study at 60. We allocated 30 patients to the intervention group and the remaining 30 to the placebo group.

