### Data Analysis

Data analyses will be performed using SPSS 24.0 software. Continuous variables with a normal distribution will be analyzed using Student *t* test, while nonnormally distributed variables will be analyzed using the Wilcoxon rank sum test. Categorical variables will be analyzed using Pearson *χ*^2^ test. Continuous variables will be presented as mean (SD), while categorical variables will be presented as percentages. Values with *P* values ≤.05 will be considered statistically significant, and all tests will be 2-sided.

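### The t test or rank sum test planned for time to bowel sound recovery and time to first defecation cannot use a patient who dies or leaves before the event, and no stated missing-data rule restores that patient when withdrawal is low

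*Protocol article*

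**What the plan says.** Other Measures, a subsection of Secondary Outcomes in the protocol article, introduces the bowel-recovery measures with "These include the time to bowel sound recovery, time to first defecation, and the gastrointestinal function score". It gives no time origin, no observation window and no score for a patient in whom the event is not seen.

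Data Analysis fixes the methods. "Continuous variables with a normal distribution will be analyzed using Student *t* test", and "nonnormally distributed variables will be analyzed using the Wilcoxon rank sum test". The summary is also fixed: "Continuous variables will be presented as mean (SD), while categorical variables will be presented as percentages". The only other test named is Pearson chi-square, for categorical variables.

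Sample Size treats another time to recovery in the same way. It uses a formula for two means and one SD, and explains: "We used the time blood amylase took to return to normal levels to determine the clinical efficacy of the decoction".

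Three sections deal with incomplete data:
- **Withdrawal Cases:** at low withdrawal, "If the rate is <5%-10%, we will perform data cleaning". Above 10% it foresees imputation, intention-to-treat and sensitivity analysis, without naming a method. It says that a patient who discontinues the intervention is no longer included, yet also that data gathered up to that point stay in the analysis.
- **Management of Dropout Cases:** keeps the data of treated patients for the intention-to-treat analysis.
- **Data Management and Monitoring:** mentions unspecified ways of processing missing data and a sensitivity analysis.

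**The concern.** Both outcomes are waiting times. A patient who has not defecated by the time of death or departure carries real information: the wait was at least that long, or recovery never came. A t test or a rank sum test needs one number per patient and cannot take a statement of that kind. Unless a rule supplies a number, the field stays blank and standard software omits the patient.

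If the omitted patients tend to be slow or non-recovering, the remaining comparison is conditional on having recovered. More such losses on the decoction would make it look faster than it is. More on placebo would shrink a real benefit and cost power. Improving gastrointestinal function is a stated aim in the Introduction, so these two times bear on a question the trial wants to answer, although they are not the primary outcome.

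**Working it through.** **1. Which method applies.** A time in hours is a continuous variable, so Data Analysis sends it to the t test or the rank sum test and to mean (SD). No method for censored times or for death as a competing event is named. The article gives no expected values for these two outcomes, so there is no planned figure to reproduce. The total of 60 was sized on amylase normalisation, and its means and SD are not given.

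**2. Two invented patients.** Patient A first defecates at 60 h and scores 60. Patient B still has no bowel function at death on day 5. B did worse than A, but the stated methods have a value for A and none for B. Withdrawal Cases says to keep B's data, but what was collected on B is a censored time, which those methods cannot use.

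**3. How many patients could be affected.** Inputs: 60 patients (Sample Size), about 20% progressing to severe disease and 20%-40% mortality in severe disease (Introduction).
- Lower: 60 × 0.20 × 0.20 = 2.4 deaths, or 4%.
- Upper: 60 × 0.20 × 0.40 = 4.8 deaths, or 8%.
- The 10% withdrawal threshold: 60 × 0.10 = 6 patients.

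Deaths alone would therefore stay in the range where the only stated step is data cleaning; whether a death counts as a withdrawal is not stated. Only deaths before bowel recovery matter. Withdrawals add to the count, but no rate is given. The background rates are for acute pancreatitis in general, whereas this trial recruits from intensive care.

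**4. When losses fall on the slowest patients of one arm.** Assumptions, none from the article: log-normal times, median 72 h, coefficient of variation 0.6, 30 per arm, two-sided rank sum test at .05, 6,000 simulated trials per row.

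| True effect | Slowest patients lost | Rejection rate if dropped | Rejection rate if kept at worst rank |
|---|---|---|---|
| None | 0 | 4.8% | 4.8% |
| None | 3, one arm only | 10.6% (mean difference 11.6 h) | 3.8% |
| None | 5, one arm only | 18.7% (mean difference 16.6 h) | 3.4% |
| Times × 0.7 | 0 | 65.8% | 65.8% |
| Times × 0.7 | 3, placebo only | 45.3% | 66.8% |
| Times × 0.7 | 5, placebo only | 32.2% | 68.4% |

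These are unfavourable cases. With equal losses in both arms the bias largely cancels.

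**5. When follow-up is complete.** Under the same distribution the log-SD is √ln(1 + 0.6²) = 0.555. Day 28 is 672 h, so z = ln(672/72)/0.555 = 4.03, and fewer than 1 in 10,000 patients would still be waiting. A second set of assumptions (medians 48 h and 33 h, log-SD 0.6) treats patients as unseen after a cut-off:

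| Last hour observed | Mean difference if unseen are dropped (true: about 18 h) | Power, dropped | Power, kept at worst rank |
|---|---|---|---|
| 72 | 7.5 h | 0.37 | 0.63 |
| 96 | 10.5 h | 0.50 | 0.64 |
| 168 | 15.9 h | 0.62 | 0.64 |
| 672 | 18.0 h | 0.63 | 0.63 |

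The harm comes from early loss, not from the test as such.

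**6. When losses are unrelated to the bowel course.** With equal medians of 48 h and random losses of 20% and 5%, dropping leaves the rank sum rejection rate at 4.7%, while giving every lost patient the worst rank raises it to 16.3%. A worst rank for every kind of loss is therefore not harmless.

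**The case against.** The strongest reply is that nothing in the article says a patient without the event is dropped. Data before withdrawal are retained, treated patients are kept for intention-to-treat, imputation is foreseen above 10% withdrawal, and sensitivity analysis is promised. Censoring rules for minor outcomes are also commonly left to a statistical analysis plan, which is not shown. Much of this stands. Loss of these patients is an inference from the named methods, not a rule of the plan. But the article does more than stay silent: it fixes the tests and the summary, and these do not suit the outcome. The retained data of an unrecovered patient have no place in them.

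A second reply is that 28 days of follow-up will see nearly every recovery. That holds for patients who stay. Treatment lasts 48 hours, Adverse Events advises stopping the decoction when any adverse event occurs, and Withdrawal Cases says those who discontinue are no longer included. Exits may thus come early, while the events are being timed. The article describes the placebo as free of side effects, so drug-related exits could fall mainly in one arm. How many there will be is not known.

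A reader might go further in four ways that the documents do not support:
- **The worst courses are certainly removed.** A patient may also leave for reasons unrelated to bowel function; stopping treatment for complete remission is expressly not a dropout.
- **These times are the secondary outcome named in the Abstract.** That wording matches the separate section on gastrointestinal dysfunction treatment effect. The two times stand only in Other Measures and have no row in Table 2.
- **Bowel sound recovery is timed in every patient.** Eligibility does not require impaired bowel sounds, but Other Measures does not say that all patients are timed.
- **The false-positive rates of 11% and 19% are what to expect.** They assume that exactly the slowest patients are lost, from one arm only.

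**Conclusion.** The point holds in a limited form. The stated tests cannot use a patient who dies or leaves before the event, and no section supplies a method that restores such patients when withdrawal is low. They may be lost, with bias or loss of power if losses differ by arm or concentrate in slow courses.

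The size cannot be determined from the article. Its rates give 2.4 to 4.8 deaths in all, of which an unknown part precede bowel recovery, plus an unstated number of withdrawals. Every simulated figure rests on assumed distributions and loss patterns. If follow-up to day 28 is complete and losses are balanced, the effect is small. The matter concerns secondary measures and leaves the primary outcome untouched, but a better-suited method costs little.

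**What to change.** Add to Data Analysis: both times run from the first dose in all randomised patients; a patient without the event is censored at the last observation if alive; death before the event is a competing event; arms are compared by cumulative incidence with Gray's test, and medians with 95% confidence intervals are reported.

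A simpler alternative keeps the rank sum test already named and gives patients who die without the event the worst rank. Living patients who leave early then still need a stated rule, and step 6 shows why the worst rank should not be extended to them automatically.

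Restrict bowel sound recovery to patients with reduced or absent sounds at baseline only if baseline bowel sounds were recorded. Table 2 does not schedule that record.

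The cost is a few sentences, with medians and cumulative incidence replacing mean (SD). No new data are needed provided that event times and last observation times were recorded, which the article does not confirm. Results states that data are collected and under analysis, so the change must be disclosed as made after data collection.

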## Introduction

Acute pancreatitis (AP) is a common yet potentially fatal inflammatory disorder of the pancreas, characterized by severe abdominal pain, multi-organ dysfunction, and pancreatic necrosis. The global incidence of AP is approximately 30-40 cases per 100,000 people, with over 2000 fatalities annually [1]. Severe AP (SAP), which involves persistent organ failure lasting ≥48 hours, is the most life-threatening form of AP, with a mortality rate of 20%-40% despite significant advancements in treatment [2-4]. Approximately 20% of patients with AP progress to SAP, which is associated with severe complications such as organ failure, infections, and increased health care costs [1,5].

The pathophysiology of AP is characterized by premature activation of trypsin within the pancreatic acinar cells, triggering pancreatic autodigestion and leading to a systemic inflammatory response. This response results in systemic inflammatory response syndrome, which can progress to multi-organ dysfunction syndrome [6,7]. Although the treatment of AP is mainly supportive, including fluid resuscitation and organ support, there remains a lack of consensus on the optimal management protocols for fluid therapy [8,9], and strategies to promote gastrointestinal recovery remain limited [10].

In addition to conventional Western treatments, Chinese herbal medicines have gained attention for their potential in managing AP. Chinese herbal medicines are known for their ability to target multiple biological pathways involved in inflammation, immune response, and organ protection, offering a broader approach compared to single-target Western therapies [11,12]. DaXianXiong decoction, a traditional herbal formula used in China for over 30 years, has been reported to improve gastrointestinal symptoms and modulate inflammation. However, its clinical efficacy in preventing the progression of AP to SAP has not been conclusively demonstrated due to the lack of robust randomized controlled trials [12-14].

In light of these challenges, there is an urgent need for high-quality studies to evaluate the efficacy and safety of DaXianXiong decoction in the treatment of AP. This study aims to assess the potential of DaXianXiong decoction in preventing the progression of AP to SAP, reducing inflammatory markers, improving gastrointestinal function, and assessing safety and complications.

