### Outcome Measures

The outcome measures will be determined at various time points throughout the study, including baseline (T0, before treatment), 24 hours after the final treatment (T1, end point 1), 3 days after the final treatment (T2, end point 2), 7 days after the final treatment (T3, end point 3), and 28 days after the final treatment (T4, final end point). The data collection and assessment schedule are listed in Table 2.

**Table 2 table2:** The data collection and assessment schedule.

Assessments		Study period				Follow-up		
		Enrollment and allocation (T0)	Intervention (48 hours)	Primary end point (T1)	T2		T3	T4

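### Hospital duration and the severity scores have no rule for patients who die, so these secondary and other outcomes can favour an arm with more early deaths

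*Protocol article*

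**What the plan says.** All references are to the protocol article.

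- **Other Measures:** "We will also record hospitalization costs and duration". No rule is given for a patient who dies in hospital.
- **APACHE II Score:** "APACHE II = (original score – current score)/original score × 100" percent. The modified CT severity index and the inflammation factors are defined the same way, each needing a current value.
- **Outcome Measures and Table 2:** the modified Marshall score, CT severity index, APACHE II and inflammation markers are scheduled from T1 through T4, which is 28 days after the last dose. Hospitalization and survival are separate items at T4.
- **Data Analysis:** a *t* test applies where the distribution is normal. For the rest, the rule is that "nonnormally distributed variables will be analyzed using the Wilcoxon rank sum test". Continuous variables are summarised by mean and SD.
- **Withdrawal Cases, Management of Dropout Cases, Data Management and Monitoring:** these cover withdrawal, loss to follow-up and unavoidable missing data. Below about 10% withdrawal the response is data cleaning; above 10% it is imputation, intention-to-treat and sensitivity analysis. None of them mentions death.
- **Introduction:** "Approximately 20% of patients with AP progress to SAP", and severe disease is described "with a mortality rate of 20%-40% despite significant advancements in treatment".

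**The concern.** Death affects these outcomes in two ways. For a score at T2, T3 or T4, a patient who has died has no current value, so the percent-change formula cannot be evaluated and the comparison is among survivors. For duration, a patient who dies early contributes a short stay, which reads as a better result than a survivor's long one. Cost can behave the same way.

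If one arm has more early deaths, its mean stay and its survivors' mean score can both look better because of those deaths. The abstract lists the severity scores among the primary outcomes, although the Methods section names only the incidence of severe acute pancreatitis, so the scores may carry weight in the report.

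**Working it through.** The plan prints no figure on this point to reproduce. Its sample size of 60 cannot be rebuilt, because the means and SD behind it are not given, and the point does not depend on it.

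**1. Expected deaths (Introduction rates; 60 patients, 30 per arm)**
- Overall risk = 0.20 × 0.20 to 0.20 × 0.40 = 4% to 8%.
- Deaths = 60 × 0.04 to 60 × 0.08 = 2.4 to 4.8, or 1.2 to 2.4 per arm.
- Chance of at least one death = 1 − 0.96^60 = 91% to 1 − 0.92^60 = 99%.
- Patients come from an intensive care unit. If 40% to 60% developed severe disease (assumed), expected deaths would be 60 × 0.40 × 0.20 = 4.8 to 60 × 0.60 × 0.40 = 14.4.

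**2. Would the missing-data text catch this?** Even if deaths were counted as withdrawals, 4% to 8% is below the 10% trigger, so the stated response is data cleaning. Above the trigger, imputation would supply a score that a deceased patient never had.

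**3. Chance imbalance.** With equal true risk of 4% to 8% and two independent binomial arms of 30, the arms differ by at least one death with probability 72% to 81%, by at least two with 30% to 46%, and by at least three with 9% to 23%.

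**4. Shift in mean stay.** Assumed: 10 days without severe disease, 25 days for survivors of severe disease, death at day 5, and 20% severe disease in both arms. Let *m* be mortality in severe disease.
- Mean = 0.8 × 10 + 0.2 × [(1 − *m*) × 25 + *m* × 5].
- *m* = 20%: 8 + 0.2 × (20 + 1) = 12.2 days.
- *m* = 40%: 8 + 0.2 × (15 + 2) = 11.4 days.
- The arm with more deaths looks 0.8 days better. With death at day 20 the means are 12.8 and 12.6, a gap of 0.2 days. With death at day 5 and severe-disease rates of 40% and 60%, the gap is 1.6 and 2.4 days.
- An unfavourable case: three extra deaths at day 5 in place of 20-day stays (assumed) lower one arm's mean by 3 × (20 − 5)/30 = 1.5 days.

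**5. The same stays as days alive and out of hospital.** From first dose to T4 is about 2 + 28 = 30 days. With death = 0:
- *m* = 20%: 0.8 × 20 + 0.2 × 0.8 × 5 = 16.8 days.
- *m* = 40%: 0.8 × 20 + 0.2 × 0.6 × 5 = 16.6 days.
- The false advantage is gone.

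**6. Scores.** Assumed late score (the score itself, for simplicity): 4 without severe disease, 8 in survivors of severe disease.
- Survivors only, *m* = 20%: (0.8 × 4 + 0.16 × 8)/0.96 = 4.67.
- Survivors only, *m* = 40%: (0.8 × 4 + 0.12 × 8)/0.92 = 4.52. The arm with more deaths looks better.
- With an assumed worst score of 20 for deaths: 3.2 + 1.28 + 0.04 × 20 = 5.28 against 3.2 + 0.96 + 0.08 × 20 = 5.76. The order reverses.

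**The case against.** The strongest reply is that this is an omission, not an error. How deaths enter secondary outcomes is often left to a full protocol or analysis plan, neither of which is shown. The article says only that cost and duration are recorded. It nowhere says that deceased patients are dropped, and it promises a sensitivity analysis for missing data.

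That limits the point but does not remove it. The article does fix a percent-change formula and one test rule for all continuous variables. Followed as written, they give no value for a deceased patient and count an early death as a short stay.

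A reader might go further and infer that the plan makes mortality look like benefit, or hides it. The documents do not support that:
- The distortion needs deaths that differ between arms in number or timing. With equal mortality and similar timing, neither arm gains systematically.
- A death need not mean a short or cheap stay; a late death in intensive care can be long and costly.
- Survival is collected at T4, so deaths can be shown, although no outcome section commits to showing them beside these results.
- Three excess deaths in one arm is an unfavourable case, not the expected one.

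Reporting survivors' values beside deaths per arm would also be defensible. A composite with death is a choice with its own cost.

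**Conclusion.** The point holds in conditional form, as a low-cost improvement. As written, the late scores become survivors-only comparisons and an early death counts as a short stay; nothing in the missing-data text corrects this. On the Introduction's rates, 2.4 to 4.8 deaths are expected in 60 patients.

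The likely shift in mean stay is under about 1 day at those rates: 0.8 days with death at day 5 and 0.2 days with death at day 20, for 20% against 40% mortality in severe disease. Larger shifts need an assumed higher rate of severe disease or an unfavourable imbalance. All stay and score values are assumptions; only the rates of severe disease and death, the follow-up times and the sample size come from the article.

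The outcomes affected are secondary or other measures under the Methods section. The primary outcome named there is not affected by this mechanism. The abstract's different list of primary outcomes is a separate inconsistency.

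**What to change.** State the handling of death before any unblinded analysis. The Results section says data are already collected and being analysed, so label the rule as added at this stage.

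- **Duration:** analyse days alive and out of hospital over the follow-up to T4, with death = 0, or analyse duration with deaths ranked worst.
- **Scores at T2 to T4:** give patients who have died by that visit the worst rank and compare arms with the Wilcoxon rank sum test already in the Data Analysis section, whether or not survivors' values look normal.
- **Reporting:** show survivors-only scores and costs as descriptive, beside the number of deaths in each arm.
- **Inflammation markers:** say whether they follow the same rule, since they use the same percent-change formula.

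The cost is a few sentences of analysis wording. No new data are needed, because hospitalization and survival are already scheduled at T4. The downside is that these outcomes become composites with death and are less direct to read; the descriptive survivors-only values partly offset that.
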